## Discussion

3

The present study is expected to provide robust evidence regarding the efficacy and safety of combining opposing needling with electroacupuncture for KOA. By testing the hypothesis that this combination may produce additive or synergistic analgesic effects, the trial aims to elucidate the therapeutic value of integrating these two classical acupuncture techniques. A rigorous three-arm parallel-group design will be employed, including an OE group, a SE group, and an EA group. On one hand, this design allows for the evaluation of the additive effect of opposing needling as well as the overall therapeutic benefit of the combined intervention; on the other hand, both the OE and SE groups receive bilateral needling, which helps reduce the risk of unblinding. In addition, the trial incorporates a comprehensive set of outcome measures, enabling a multidimensional assessment of the therapeutic effects of opposing needling plus electroacupuncture. Finally, the study emphasizes standardization and reproducibility of the intervention: all treatments will be administered by uniformly trained acupuncturists, and quality control and monitoring procedures are established to ensure intervention consistency and internal validity of the results.

Nevertheless, certain limitations remain. The follow-up period is limited to 12 weeks, allowing only preliminary evaluation of efficacy and precluding assessment of long-term effects in KOA; future studies should consider extending the follow-up duration. In addition, this is a two-center study with a relatively small sample size. Larger and multicenter RCTs will be required to further validate the generalizability and external applicability of the findings.

Overall, the results of this study are expected to strengthen the clinical evidence for acupuncture-based management of KOA, inform treatment optimization, and provide a foundation for future research on innovative needling techniques in chronic pain management.

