**Methods:**

This two-center randomized controlled trial will enroll 108 eligible patients with KOA, who will be randomly assigned in a 1:1:1 ratio to opposing needling plus electroacupuncture, sham opposing needling plus electroacupuncture, or electroacupuncture alone. The 12-week study comprises an 8-week intervention period and a 4-week follow-up, with treatments administered three times per week. The primary outcome will be the Western Ontario and McMaster Universities Osteoarthritis Index (WOMAC), while secondary outcomes will include WOMAC subscales, Visual Analog Scale, Numeric Rating Scale, Global Pain Scale, Lequesne Index, Knee Injury and Osteoarthritis Outcome Score, and Short Form-36 Health Survey.

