Opposing needling, a classical technique involving contralateral acupoints with deep insertion along meridians, is primarily indicated for pain (21, 22) and has documented efficacy in various chronic pain disorders (23–27). From the perspective of traditional Chinese medicine, opposing needling emphasizes the concept of bodily integrity. When the flow of qi and blood along the meridians is obstructed and the left–right balance is disrupted, the meridian function on the affected side is weakened while the healthy side remains normal. Therefore, acupuncture at the corresponding points on the healthy side can stimulate the flow of qi, promote circulation of blood and qi, eliminate pathogenic factors, and restore the function of the affected meridians, achieving a dynamic balance of “yin and yang” between both sides of the body. From the perspective of modern medicine, studies have demonstrated that opposing needling can effectively relieve pain through protective inhibition of the cerebral cortex, reflex regulation via the nervous and humoral systems, and interruption of local nociceptive stimuli. The signals generated by acupuncture not only modulate pain transmission through spinal segmental connections but also promote the release of multiple endogenous analgesic substances, thereby increasing pain thresholds and activating descending inhibitory signals from higher centers. These combined effects contribute to the improvement of local pain and provide comprehensive pain management (28).

Previous studies suggest that opposing needling may enhance therapeutic outcomes in KOA, either alone or combined with other treatments (29–32). This indicates that opposing needling not only exerts an independent analgesic effect but may also play an adjunctive role. Therefore, we propose a reasonable hypothesis that combining opposing needling with electroacupuncture may produce additive or synergistic analgesic effects based on the analgesic action of electroacupuncture.

Given the independent and potential synergistic effects of opposing needling, we designed a sham-controlled, two-center randomized trial to evaluate the efficacy and safety of opposing needling as an adjunct to electroacupuncture in KOA patients. The study implements improved control procedures, comprehensive outcome measures, and refined group allocation to provide robust evidence and novel insights for clinical management.

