**Figure 2 fig2:**
[figure not shown]
Acupuncture point diagram. Screenshot from the mobile application ‘Zhiyuan Meridian and Acupoint’ (知源经络穴位) (https://apps.apple.com/app/id1554030035), with local knee acupoints labeled by the authors. Copyright permission for academic use has been obtained.

This trial will use Chinese HWATO stainless steel filiform needles (0.30 mm × 25 mm and 0.30 mm × 40 mm) and the Chinese HWATO SDZ-III Low-Frequency (1–100 Hz) Pulse Electronic Acupuncture Stimulator Machine, with 6 channels, and adjustable output power (0.3–10 V at 250 ohms).

Prior to the procedure, the acupuncturists will wash their hands with antiseptic hand sanitizer and disinfect the skin at each acupoint site using a 75% alcohol swab in a circular motion from the center outward. Needle insertion depth will be determined based on the specific anatomical characteristics of each acupoint. The twisting technique will be used to elicit Deqi sensation, characterized by soreness, numbness, heaviness, distension, warmth, coolness, or the transmission of needling sensation, while the acupuncturists perceive resistance or tension beneath the needle.

Once Deqi sensation is achieved, a twirling-rotating method with even manipulation will be applied using a twisting angle of approximately 180° at a frequency of 120–160 times per minute. Electroacupuncture will be applied to the more affected knee for 30 min. Two pairs of output wires will be connected: one pair from Liangqiu (ST34, anode) to Yanglingquan (GB34, cathode) on the lateral side, and another from Yinlingquan (SP9, anode) to Xuehai (SP10, cathode) on the medial side. A dense-disperse wave of 2/100 Hz will be selected, and the electrical current will be gradually increased until the patient experiences a mild, rhythmic muscle twitching around the acupoints without discomfort.

After 30 min of stimulation, the acupuncturists will press a dry cotton ball around the needle site with one hand and simultaneously rotate and withdraw the needle slowly with the other hand. Gentle pressure will be applied to the insertion site to prevent bleeding.

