#### Electroacupuncture alone

2.6.3

The more affected side will receive acupuncture treatment following the same needling procedures, acupoint selection, and electroacupuncture protocol as the more affected side in the OE group.

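### The trial is said to test whether opposing needling and electroacupuncture are additive or synergistic, but every arm receives electroacupuncture, so only the add-on effect can be estimated

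*Protocol article*

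**What the plan says.** The Introduction (section 1) puts forward the hypothesis that "combining opposing needling with electroacupuncture may produce additive or synergistic analgesic effects based on the analgesic action of electroacupuncture". The Discussion (section 3) treats this as what the trial examines: "By testing the hypothesis that this combination may produce additive or synergistic analgesic effects". It adds that "this design allows for the evaluation of the additive effect of opposing needling as well as the overall therapeutic benefit of the combined intervention".

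The Introduction also gives a narrower purpose for the sham-controlled design: "to evaluate the efficacy and safety of opposing needling as an adjunct to electroacupuncture in KOA patients".

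Participants are "randomly assigned in a 1:1:1 ratio to opposing needling plus electroacupuncture, sham opposing needling plus electroacupuncture, or electroacupuncture alone" (Abstract, Methods). Electroacupuncture is the same in every arm:

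- **OE** (section 2.6.1): "Electroacupuncture will be applied to the more affected knee for 30 min".
- **SE** (section 2.6.2): the more affected side is treated exactly as in OE. The sham device is used only on the contralateral side.
- **EA** (section 2.6.3): the more affected side is treated "following the same needling procedures, acupoint selection, and electroacupuncture protocol as the more affected side in the OE group".

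The limitations in the Discussion cover length of follow-up, the number of centres and sample size. They do not mention interaction.

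**The concern.** Two treatments are additive if their joint effect equals the sum of their separate effects, and synergistic if it exceeds that sum. Checking either requires the effect of opposing needling when electroacupuncture is absent. No arm here omits electroacupuncture, so the stated hypothesis concerns a quantity on which the trial collects no information.

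What is at stake is the conclusion that may be drawn. A clear OE−SE difference would answer the adjunct question. Read against the hypothesis as worded, it could also be taken as support for additivity or synergy, although the same difference would arise if the two treatments partly duplicated each other.

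**Working it through.** **Inputs.** The arm contents are those of sections 2.6.1 to 2.6.3. Section 2.3 assumes mean changes in total WOMAC at week 8 of −32.3 (OE), −22.42 (SE) and −8.87 (EA); more negative is better. The plan gives no figure for an interaction, so there is none to reproduce. The sample size per group does not bear on this point.

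**Step 1: what each arm contains.** Let μ be the mean change with neither treatment, E the effect of electroacupuncture alone, N the effect of real opposing needling alone, I the interaction of the two, and S the non-specific effect of an extra contralateral procedure.

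- OE = μ + E + N + I + S
- SE = μ + E + S
- EA = μ + E

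**Step 2: what the contrasts estimate.**

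- OE − SE = N + I
- SE − EA = S
- OE − EA = N + I + S

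E cancels from every contrast, and N and I appear only as a sum. The three-arm design matrix has rank 3 for five parameters. A rank check confirms that I, N, E and the combination against no treatment (E + N + I, with or without S) are not estimable, whereas N + I and S are. The same holds if the OE arm is assumed to carry no S component. A four-cell layout (both, electroacupuncture only, opposing needling only, neither) has rank 4, and there both I and E + N + I become estimable. The obstacle is therefore the set of arms, not the number of participants.

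**Step 3: the planned differences.**

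- OE − SE = −32.30 − (−22.42) = −9.88
- SE − EA = −22.42 − (−8.87) = −13.55
- OE − EA = −32.30 − (−8.87) = −23.43
- Share of OE − EA that is the assumed SE − EA difference: 13.55 / 23.43 = 58%

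**Step 4: what −9.88 says about interaction.** Since N + I = −9.88, I = −9.88 − N. The trial never observes N, so the values below are assumed purely for illustration.

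| Assumed N | I = −9.88 − N | Reading |
|---|---|---|
| −5 | −4.88 | synergy |
| −9.88 | 0 | additivity |
| −15 | +5.12 | sub-additivity |

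All three rows predict identical results in OE, SE and EA.

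**The case against.** The strongest reply is that the operative objective is already the right one. The Introduction states an adjunct purpose, and the three arms serve it. No interaction test is planned in the sample size, primary outcome or statistical analysis sections, and nowhere does the article promise to tell additivity from synergy. The additive effect of opposing needling, as the Discussion puts it, can fairly be read as the add-on effect, which is estimable. All of this stands, and it limits the point to the stated hypothesis and the conclusions drawn from it. It does not rescue the claim of synergy, which appears in both the Introduction and the Discussion and is described as being tested. Even the looser pairing, additive or synergistic, excludes sub-additivity, which the design cannot do.

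A reader might infer three stronger things that the document does not support.

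- **That the overall benefit of the combination has no comparator.** It has one if read as OE−EA, a randomised contrast, and the Discussion does not say that benefit over no treatment is meant.
- **That efficacy will be judged from uncontrolled change within the OE arm**, with natural course, selection on pain and rescue medication mixed in. Section 2.7 speaks of effects across the groups and section 2.12 analyses efficacy by analysis of covariance. Change from baseline is the outcome variable; within-arm change is not stated as the test of efficacy.
- **That the primary comparison is invalid or an arm must be added.** Neither follows, because the add-on question is answerable with the arms as they are.

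**Conclusion.** The point holds as a mismatch between the stated hypothesis and the design. Interaction, and hence additivity or synergy, is not identifiable from OE, SE and EA at any sample size. This follows from the arm definitions and does not depend on the assumed means. The planned OE−SE difference of 9.88 WOMAC points is compatible with interaction in either direction or none.

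The adjunct trial is intact. OE−SE estimates the specific add-on effect of real over sham opposing needling on top of electroacupuncture, provided the non-specific effect of the contralateral procedure is the same in both arms. OE−EA estimates the total gain over electroacupuncture alone and includes that non-specific effect: on the plan's own assumptions, 13.55 of 23.43 points (58%). Additivity is taken here on the scale of mean WOMAC change. The stand-alone effects of 5 and 15 points are illustrations, not estimates.

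**What to change.** 1. In the Introduction and the Discussion, restate the hypothesis as: whether real opposing needling improves week-8 WOMAC more than sham opposing needling when both are added to electroacupuncture. Delete the additive-or-synergistic wording in both places.
2. In the Discussion, define the overall therapeutic benefit of the combined intervention as the OE−EA contrast, relative to electroacupuncture alone and including non-specific effects of the extra procedure.
3. Add to the limitations that the trial can assess neither the interaction between the two treatments nor the benefit of the combination over no treatment.

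This changes text only: no arm, participant, assessment or analysis is added. The downside is a narrower claim.
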